## METHODS

2

### Trial design

2.1

SUCCEAT is a two‐arm multicentre, parallel group RCT with a nonrandomised control group (see Figure 1). Incoming patients are screened for AN or atypical AN and are randomly allocated to the Intervention group 1 (workshop support groups) or the Intervention group 2 (web‐based support groups), respectively, in addition to treatment as usual (TAU), and compared with a nonrandomised control group (TAU). The study is conducted in Austria and Germany.

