#### Primary hypothesis—Carers

1.3.1

Carers participating in the SUCCEAT intervention groups will report a greater reduction of distress (General Health Questionnaire: Linden et al., 1996) at postintervention (T1) than the carers in the control group.

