#### Primary hypothesis—Patients

1.3.2

Patients whose carers participate in the SUCCEAT intervention groups will show a greater reduction of ED symptoms (Eating Disorder Examination: Hilbert & Tuschen‐Caffier, 2006; Eating Disorder Inventory 2: Paul & Thiel, 2005) at postintervention (T1) than the patients in the control group.

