#### Study settings and locations where the data will be collected

2.2.2

Patients and carers will be recruited at different inpatient and outpatient centres with ED units, where they receive TAU. Carers and patients who meet the eligibility criteria are invited to participate in the study. Patients and carers both give their informed consent, and parents give their informed consent for children who are minors.

Carers and patients of the two SUCCEAT intervention groups will be recruited at the Medical University of Vienna, Department of Child and Adolescent Psychiatry, and by consultant child and adolescent psychiatrists and at different centres with ED units in adjacent federal states to Vienna. Patients and carers in the two intervention groups give their informed consent and complete the questionnaires at the Medical University of Vienna, Department of Child and Adolescent Psychiatry.

For the control group, patients and their carers will be recruited and receive TAU at three centres: at the Wilhelminenspital in Vienna, Department of Child and Adolescent Medicine, Inpatient and Outpatient Unit for Children and Adolescents; at the Clinical Centre Klagenfurt, Department of Neurology and Psychiatry for Children and Adolescents; and at the Parkland‐Clinic for Psychosomatic and Psychotherapy in Bad Wildungen, Germany. Patients and carers in the control group give their informed consent and complete the questionnaires at the recruiting site.

The interventions started in November 2014 and will continue approximately until April 2018. Follow‐up assessments for the remaining patients are expected to be completed by April 2019. The main ethics approval has been granted by the Medical University of Vienna Ethics Committee (1840/2013). Site‐specific ethics approvals are granted for all participating sites.

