### Outcome measures

2.4

To describe the sample, clinical data and demographic information about the patients and their carers are collected at baseline (T0; age, sex, educational level, family situation, migration status, and socio‐economic status). Further assessments for the primary and secondary outcome measures (see Table 2) will take place before starting the intervention (T0), after 3 months (postintervention, T1), and 1 year after the intervention (follow‐up, T2). The semistructured interview of the Eating Disorder Examination (Fairburn & Cooper, 1993; German version: Hilbert & Tuschen‐Caffier, 2006) is conducted face‐to‐face or via telephone by professionals (clinical and health psychologists and psychotherapists). These professionals also administer the other questionnaires, which are answered in a paper–pencil version by the carers and patients themselves. These professionals have already been trained to use these measures before this RCT (by experienced professionals in this field) or received training by [name] prior to the study. The questionnaires for the process evaluation are answered by the carers of the SUCCEAT intervention after each workshop session or web‐based module and at T1 and T2. Table 2 and Supplement S1 contain further information about the questionnaires.

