### Randomisation

2.6

After recruitment of the patients and their carers (at the Medical University of Vienna, Department of Child and Adolescent Psychiatry, and by consultant child and adolescent psychiatrists in adjacent federal states to Vienna), patients and carers who meet the eligibility criteria give their informed consent, perform baseline assessments, and are randomly allocated to one of the two intervention groups (SUCCEAT workshop support group or SUCCEAT web‐based support group) by our research group at the Medical University of Vienna. Random allocation is made in a blockwise manner in order to keep the sizes of treatment groups similar. Incoming patients are numbered consecutively, and randomisation is done blockwise according to the consecutive numbering, in blocks of eight participants in the workshop support group and web‐based support group, respectively. The control group is not randomised.

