### Statistical analysis plan

2.8

The treatment effect will be analysed by using mixed‐design ANOVAs. The time points will be included as within group factor, and the group (workshop support group vs. web‐based support group vs. TAU) will be included as between group factor. *t* tests for dependent and independent samples will also be used in order to explore differences between specific groups and specific time points.

Two analysis strategies will be applied to account for missing data: Intention‐to‐treat analysis will be used as the primary analysis strategy. If posttreatment or follow‐up data are missing, the last‐value‐put‐forward method will be used. Additionally, the analyses will be repeated by including completers only. Completers will be defined by attending more than 50% of the workshop sessions or web‐based modules. To analyse the potential effect of treatment moderators, additional ANOVAs will be calculated including patient's age and duration of illness as covariates.

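### Both primary comparisons are against a non-randomised control from other centres, and the primary ANOVA, with only time and group, assumes without adjustment that the groups would have changed alike

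*Protocol article*

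**What the plan says.** The points below are all from the protocol article.

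- **Primary contrasts (1.3.1 and 1.3.2).** Carers in the SUCCEAT groups are expected to show a larger fall in GHQ distress at T1 "than the carers in the control group". Their patients are expected to show a larger fall in EDE and EDI-2 symptoms "than the patients in the control group". Workshop versus web is a secondary hypothesis (1.3.3).
- **Allocation (2.1 and 2.6).** Only the two SUCCEAT formats are randomised. Section 2.1 has them randomly allocated "and compared with a nonrandomised control group (TAU"; section 2.6 states "The control group is not randomised".
- **Sites (2.2.2).** "Carers and patients of the two SUCCEAT intervention groups will be recruited at the Medical University of Vienna", and also through consultant psychiatrists and eating-disorder centres in the adjacent federal states. For the control group, "patients and their carers will be recruited and receive TAU at three centres": a Vienna hospital, Klagenfurt, and a psychosomatic clinic in Germany.
- **Primary model (2.8).** Time is the within factor, and the three-level group "will be included as between group factor". No covariate, centre term, matching or weighting is given. Patient age and illness duration are covariates in additional ANOVAs, whose stated aim is to examine treatment moderators.
- **Baseline data (2.4).** "To describe the sample, clinical data and demographic information about the patients and their carers are collected at baseline".
- **Limitations (3.1).** Only the unvalidated German questionnaires are discussed.

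**The concern.** The headline efficacy claims rest on a comparison between centres. Families at different centres may differ in severity, chronicity, care setting and local TAU, and each of these can alter how much carers and patients change over three months. Section 2.2.2 has inpatient and outpatient units recruiting, and section 2.2.1 lets the frequency and duration of psychological treatment follow patient need, so such differences are plausible.

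The group-by-time term answers the hypotheses as worded, because they concern reduction, and a fixed difference in level between groups cancels. A difference in expected change does not cancel. It would be reported as a SUCCEAT effect on GHQ, EDE or EDI-2, or it would hide one. Section 2.8 specifies nothing in the primary analysis to reduce it, and nothing in the limitations would warn a reader of the results.

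**Working it through.** **1. The plan's own figure.** Section 2.5 gives 0.88 power at 5% with 40 per group for a medium effect, then 48 per arm and 144 in total.

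- Assumption: medium means f = 0.25 (the article gives no number).
- Method: multivariate test of the group-by-time interaction, which suits the stated case where sphericity fails; 3 groups, 3 time points, N = 120.
- Noncentrality = f² × s × N = 0.0625 × 2 × 120 = 15, with 4 and 234 degrees of freedom. Power = 0.884, which matches the plan.
- Dropout: 40 / 0.83 = 48.2, against 48 stated; 48 × 3 = 144.

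The sample size is not in dispute. It does, however, allow for sampling error only, not for a systematic difference in change between groups.

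**2. What the primary model removes.** Write expected change from T0 to T1 without SUCCEAT as c_S for SUCCEAT families and c_C for controls, and the true effect as d. The group-by-time contrast estimates d + (c_S − c_C). Baseline levels drop out, but the term b = c_S − c_C stays. Randomisation would make b zero in expectation. Here nothing in the design or the model does so.

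**3. How large b would have to be to matter.** The documents give no value for b, so these values are assumed, in SD units of change, with no true effect. The pooled contrast is taken as 96 v 48 (2 × 48 against 48), because the hypotheses speak of the SUCCEAT groups together.

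- SE = √(1/96 + 1/48) = √0.03125 = 0.177 SD.
- Two-sided rejection rate = 1 − Φ(1.96 − b/SE) + Φ(−1.96 − b/SE).
- Three-group F test with 48 per group: noncentrality = (2/9) × b² × 144 = 32b², with 2 and 141 degrees of freedom.

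| Assumed b (SD) | Pooled 96 v 48 | Pooled 80 v 40 | Three-group F test |
|---|---|---|---|
| 0 | 5% | 5% | 5% |
| 0.1 | 8.7% | 8.1% | 7.4% |
| 0.2 | 20.5% | 17.8% | 15.6% |
| 0.3 | 39.6% | 34.1% | 30.4% |

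The 80 v 40 column uses the 40 per group that section 2.5 expects to keep.

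**4. How such a shift could arise (assumption only).** A prognostic factor present in 70% of one group and 30% of the other, which moves change by 0.5 SD, gives b = (0.7 − 0.3) × 0.5 = 0.20 SD.

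**5. What adjustment can and cannot do.** Covariates reduce the part of b due to measured case-mix. On the sites as listed, no named centre supplies both SUCCEAT and control families, so centre and local TAU coincide with group. No covariate set or weighting can separate them from SUCCEAT.

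**The case against.** The strongest defence has five parts.

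- **The design is disclosed.** The abstract and sections 2.1 and 2.6 all call the control non-randomised. This stands: nothing is hidden. What is missing is the statement that this affects both primary hypotheses; section 3.1 omits it.
- **The analysis is of change.** Stable level differences cancel, so it would be too strong to say that the model treats the groups as exchangeable in every respect. This stands too. The remaining assumption is narrower: equal change without SUCCEAT.
- **There are design safeguards.** One set of eligibility criteria applies, TAU follows the NICE guidelines in all groups, and one control centre is in Vienna. These make large differences less likely but do not make expected change equal.
- **Details belong in a separate analysis plan.** This is fair for the exact adjustment set. It is not fair for the primary model, because section 2.8 states that model and places the only covariates outside it.
- **Adjustment is no cure.** This is correct for centre and local TAU, as shown in the working. Conditioning on the T0 outcome is also debatable in non-randomised groups, since ANCOVA and change-score analyses can disagree when baselines differ. These limits argue for modest wording and for keeping the T0-outcome model as a sensitivity analysis. They do not argue for leaving measured case-mix unadjusted.

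A reader might infer from section 2.4 that baseline data serve only to describe the sample. The article does not support that: age and illness duration enter additional ANOVAs, T0 outcome values enter the mixed ANOVA as a time level, and BMI is a secondary outcome measured at T0. A reader might also take the recruiting unit as a record of care setting. It is not, because section 2.2.2 describes mixed inpatient and outpatient recruitment, including within one control site.

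**Conclusion.** The concern holds in this form: both primary contrasts are observational, the primary model adjusts for no confounder, and the limitations do not say so. That much rests on the text alone.

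The size is illustrative. It assumes a shift in change of 0.1 to 0.3 SD, no true effect, and independent families. On those terms the pooled contrast would be falsely significant in about 9% to 40% of trials, and the three-group F test in about 7% to 30%. The documents do not show that any such bias exists, and they do not show its direction; it could equally mask a benefit. The figures should therefore not be read as the trial's actual error rate, nor as evidence that the result will favour SUCCEAT.

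The randomised comparison of workshop with web is not affected.

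**What to change.** **Analysis (2.8).** Make the primary SUCCEAT-versus-control estimate of T0-T1 change adjusted for baseline variables the trial already holds: patient age, sex, AN versus atypical AN, illness duration, T0 BMI and socio-economic status. Add care setting at T0 only if it is recorded for each patient; section 2.4 does not list it.

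**Sensitivity analyses.** Report:

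- a propensity or overlap-weighted estimate;
- an estimate that also conditions on the T0 outcome;
- an estimate that omits the German centre. This leaves fewer than 48 controls and the same aliasing of centre with group.

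**Wording (2.8, limitations and conclusions).** State that both primary contrasts are observational, that workshop versus web is the only randomised comparison, and that centre and local-TAU effects are aliased with group and remain after adjustment.

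**Cost.** A little more analysis work and a more modest conclusion. No new participants or visits are needed.

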**Figure 1 erv2600-fig-0001:**
[figure not shown]
Diagram of the trial design of the intervention: Supporting Carers of Children and Adolescents with Eating Disorders in Austria

### Participants

2.2

#### Eligibility criteria for participants

2.2.1

The following are the inclusion criteria for children and adolescents:
Age between 10 and 19 yearsDiagnosis of AN (F50.0) or atypical AN (F50.1) according to the *International Classification of Diseases* (World Health Organization, 1990)Fluent German in order to answer outcome questionnairesAbility to provide informed consentChildren and adolescents have to receive TAU according to the NICE guidelines (NICE, 2017). TAU is multidisciplinary, coordinated between services, and includes psychological treatment, psychoeducation, and monitoring of weight, mental, and physical health. Psychological treatment for children and young people includes sessions without and together with their family members (for further information, see Section 2.3.2). The frequency and duration of the psychological treatment for the patients depend on their needs. Dietary counselling and medication for the patients are only offered as part of a multidisciplinary approach. For patients with an acute mental health risk, psychiatric inpatient care is considered. Patients whose physical health is severely compromised are admitted to inpatient or day‐patient service for medical stabilisation and to initiate refeeding, if these cannot be done in an outpatient setting.

The following are the exclusion criteria for children and adolescents:
Severe comorbidity at baseline (e.g., psychosis)No main carer (e.g., live in a children's home with no contact to own family)

The following are the inclusion criteria for main carers who complete outcome assessment:
Ability to provide informed consentThe main carer has to speak German fluently in order to answer the outcome questionnaires. The main carer is the one who spends the most time with the patient. Only the main carer will answer the questionnaires about the outcome measures. Besides the main carer, other family members and carers are also invited to take part in the intervention.

The following are the exclusion criteria for main carers:
Severe morbidity at baseline, which prevents carers from participating in the RCT (e.g., acute inpatient treatment because of physical illness)Carers without internet access (85% of Austrian and 92% of German households have internet access; European Commission, 2016)

#### Study settings and locations where the data will be collected

2.2.2

Patients and carers will be recruited at different inpatient and outpatient centres with ED units, where they receive TAU. Carers and patients who meet the eligibility criteria are invited to participate in the study. Patients and carers both give their informed consent, and parents give their informed consent for children who are minors.

Carers and patients of the two SUCCEAT intervention groups will be recruited at the Medical University of Vienna, Department of Child and Adolescent Psychiatry, and by consultant child and adolescent psychiatrists and at different centres with ED units in adjacent federal states to Vienna. Patients and carers in the two intervention groups give their informed consent and complete the questionnaires at the Medical University of Vienna, Department of Child and Adolescent Psychiatry.

For the control group, patients and their carers will be recruited and receive TAU at three centres: at the Wilhelminenspital in Vienna, Department of Child and Adolescent Medicine, Inpatient and Outpatient Unit for Children and Adolescents; at the Clinical Centre Klagenfurt, Department of Neurology and Psychiatry for Children and Adolescents; and at the Parkland‐Clinic for Psychosomatic and Psychotherapy in Bad Wildungen, Germany. Patients and carers in the control group give their informed consent and complete the questionnaires at the recruiting site.

The interventions started in November 2014 and will continue approximately until April 2018. Follow‐up assessments for the remaining patients are expected to be completed by April 2019. The main ethics approval has been granted by the Medical University of Vienna Ethics Committee (1840/2013). Site‐specific ethics approvals are granted for all participating sites.

### Treatment arms

2.3

#### 
SUCCEAT intervention

2.3.1

The SUCCEAT intervention consists of eight weekly workshop sessions and web‐based modules respectively (see Table 1 for content), a SUCCEAT workbook, and the DVD *How to Care for Someone with an Eating Disorder* (The Succeed Foundation, 2011; German translation by our research group). The SUCCEAT workshop support groups and SUCCEAT web‐based support groups consist of the same content and are designed to encourage the carers to read the materials, watch the DVD, and try new behaviours as “experiments” at home. The contents of the intervention and the DVD were translated into the German language and adapted to a German‐speaking cultural context (e.g., German names of actors and meals and topics of the conversations: lyrics from a German singer) prior to the study by the SUCCEAT research group. The audio track of the DVD *How to Care for Someone with an Eating Disorder* (The Succeed Foundation, 2011) has been synchronised to the German language, and the texts have been translated. Almost all of the scenes in the DVD show young patients who still live with their parents. Therefore, the DVD is applicable to the carers of adolescent patients in our RCT. One scene shows a young adult patient (who already lives with her partner), but the content of the scene (over‐exercising) is also applicable to patients who are minors. Carers of patients with ED (who were not included in the study) tested the German materials prior to the study and gave us feedback. The DVD shows examples for communication with HEE and the same scenarios with good communication incorporating change (e.g., a family with a child with AN in a restaurant and shopping for food with a daughter suffering from AN).

Both intervention groups (workshop support groups and web‐based support groups) will involve six subgroups. Each subgroup will include the carers of about eight patients. The same two professional SUCCEAT coaches guide all the carers in each of the SUCCEAT workshop support groups and in the SUCCEAT web‐based support groups. One coach is a consultant psychiatrist, child and adolescent psychiatrist, and psychotherapist; and the other coach is a senior registrar in child and adolescent psychiatry and a psychologist. The two coaches were trained in a 2‐day workshop by [name] (e.g., Salerno, Rhind, Hibbs, Micali, Schmidt, Gowers, Macdonald, Goddard, Todd, Tchanturia, et al., 2016b), who is experienced in working with carers of patients with ED applying “The New Maudsley Method” (Treasure et al., 2010; Treasure, Smith, et al., 2007).

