##### SUCCEAT Intervention group 1—Workshop support groups for carers

All SUCCEAT workshop support groups are held at the Medical University of Vienna, Department of Child and Adolescent Psychiatry, once in a week in the evening (from 6 p.m. to 8 p.m.) and consist of eight weekly workshop sessions (see Table 1). Carers receive the SUCCEAT workbook as a hardcopy and the DVD (The Succeed Foundation, 2011; German translation of our research group) at the first workshop session. The two SUCCEAT coaches present the contents of the SUCCEAT intervention listed in Table 1 with a PowerPoint presentation and support the carers personally during the sessions. In each session, the carers will get a hardcopy handout with a summary of the workshop session. The workshops are designed to be interactive with role plays and group work for the carers. The carers are encouraged to talk about their concerns and experiences with each other. They have time to report their “experiments” and to reflect together.

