##### SUCCEAT Intervention group 2—Web‐based support groups for carers

All the carers get to know the two SUCCEAT coaches and the other participating carers of their web‐based support group personally in a welcome meeting at the beginning of the intervention at the Medical University of Vienna, Department of Child and Adolescent Psychiatry, and subsequently complete the programme at home via Internet. The web‐based support groups consist of eight weekly web‐based modules (see Table 1). The SUCCEAT web‐based modules and the SUCCEAT workbook are available on a website within a structured program (http://www.succeat.at). The formal conditions are introduced at the welcome meeting, and the carers receive the DVD (The Succeed Foundation, 2011; German translation of our research group). Carers get access to one new web‐based module weekly. They are instructed how to work on the program at any time. Within the modules, carers fill in interactive fields of the exercises and report on their experiences and the “experiments” they carried out at home. In addition, carers are invited to use the opportunity to contact the coaches via a personal message system on the website. The coaches offer their support and give weekly feedback to the exercises and the “experiments” of the carers via the personal message system. The carers have the additional possibility to communicate with the other carers and to discuss different topics in an unguided online forum on the website. This online forum is controlled regularly by the coaches and the coaches delete disturbing comments.

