### Sample size calculations

2.5

Power analysis was done with G*Power version 3.1.5. In order to detect a difference for the primary outcome (General Health Questionnaire, see Sepulveda, Lopez, Todd, et al., 2008) by calculating repeated measures analysis of variance (ANOVA; if the s*phericity* assumption is not met) at a 5% significance level with 0.88 power, carers of 40 patients per group are needed to detect medium effects (Faul, Erdfelder, Lang, & Buchner, 2007). We expect a dropout rate of about 17% (see Wagner et al., 2015). Therefore, we plan to include the carers of 48 patients per treatment arm, resulting in a total sample size of 144.

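### Families are treated in subgroups of about eight, but the planned ANOVAs, t tests and power calculation assume independence; standard errors are too small if outcomes correlate within subgroups

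*Protocol article*

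**What the plan says.** Section 2.3.1 (Treatment arms) says that each intervention format "will involve six subgroups" and that "Each subgroup will include the carers of about eight patients", so six subgroups of eight make up the 48 families per arm. On staffing: "The same two professional SUCCEAT coaches guide all the carers", in both formats.

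Carers influence one another by design. For the workshop arm: "The workshops are designed to be interactive with role plays and group work for the carers". Web carers meet their group at a welcome session and are then able "to communicate with the other carers and to discuss different topics in an unguided online forum on the website".

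Section 2.8 (Statistical analysis plan): "The treatment effect will be analysed by using mixed‐design ANOVAs". The factors are time and the three-level treatment group. Dependent and independent t tests are added, and age and illness duration enter as covariates in moderator analyses. No subgroup term, multilevel model or robust variance is mentioned.

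Section 2.5 (Sample size calculations) states that for 0.88 power at the 5% level and a medium effect, "carers of 40 patients per group are needed". The number is raised to 48 per arm (144 in total) for a dropout of about 17%, and for nothing else.

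**The concern.** People treated together for eight weeks tend to have correlated outcomes, through group dynamics, shared discussion and a common calendar period. An ANOVA or t test with the family as the unit counts each family as a full independent observation. With positive correlation the variance of an arm mean is larger than the test assumes, so p values are too small, confidence intervals too narrow and the stated power too high.

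The control group has no SUCCEAT subgroups, so the effect differs by contrast. It is largest for workshop versus web, where both sides are clustered. That is the only randomised comparison (sections 2.1 and 2.6), though a secondary hypothesis (section 1.3.3). It is smaller for SUCCEAT versus control, which carries both primary hypotheses (sections 1.3.1 and 1.3.2).

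**Working it through.** **Inputs.** From the article: subgroup size m = 8; six subgroups per format; 48 recruited and 40 analysed per arm, so m = 40/6 = 6.67 after dropout; alpha 0.05; power 0.88; three time points; three groups. Assumed: medium means f = 0.25 (no number is given), and ICC = 0.02, 0.05 or 0.10 (none is given).

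**1. The plan's own figures.** Section 2.5 names a repeated measures ANOVA without sphericity. Taking the multivariate group-by-time test with 3 groups, 3 times, N = 120 and f² = 0.0625, numerator df are 4 and denominator df about 234:
- λ = 0.0625 × 234 = 14.6 gives power 0.875.
- λ = 0.0625 × 120 × 2 = 15 gives power 0.884.

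Both round to the stated 0.88. Dropout: 40/0.83 = 48.2, against the stated 48. These figures reproduce with independent families, so no allowance for clustering is hidden in the sample size.

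**2. Standard errors.** Design effect DE = 1 + (m − 1) × ICC. With m = 8, the true standard error exceeds the assumed one by
- workshop versus web: √DE
- pooled SUCCEAT (96) versus control (48): √[(DE/96 + 1/48)/(1/96 + 1/48)] = √[(DE + 2)/3]

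The real two-sided alpha is about 2 × [1 − Φ(1.96/ratio)].

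| ICC | DE | Workshop v web: ratio, alpha | Pooled v control: ratio, alpha |
|---|---|---|---|
| 0.02 | 1.14 | 1.07, 6.6% | 1.02, 5.5% |
| 0.05 | 1.35 | 1.16, 9.2% | 1.06, 6.4% |
| 0.10 | 1.70 | 1.30, 13.3% | 1.11, 7.8% |

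**3. Simulation** (6 + 6 subgroups of 8 and 48 unclustered controls, no true effect, one outcome or change score per family, ICC 0.02 / 0.05 / 0.10):
- workshop versus web t test: about 6.5% / 9% / 13%
- pooled SUCCEAT versus control t test: about 5.6% / 6.2% / 7.6%
- three-group F test, a simple stand-in for the planned ANOVA: about 6.3% / 8.8% / 12.7%
- workshop versus web on subgroup means: about 5% throughout

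**4. Clustering in the workshop arm only.** The workshop versus web ratio becomes √[(DE + 1)/2]. At workshop ICC 0.05 this is √(2.35/2) = 1.08, alpha about 7%. At 0.10 it is √(2.70/2) = 1.16, alpha about 9%.

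**5. Power.** Take λ midway between the two values in step 1, about 14.8, which gives 0.88, and divide it by DE for m = 6.67 to 8. Power becomes about 0.83–0.84 at ICC 0.02, 0.75–0.78 at 0.05 and 0.64–0.68 at 0.10. These are lower bounds, because DE is applied to all three arms although controls are not in SUCCEAT subgroups.

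**6. Which random effect matters.** Write the outcome of a family in subgroup j as uⱼ at T0 plus noise, and uⱼ + vⱼ at T1 plus noise. The change contains vⱼ but not uⱼ. A subgroup intercept that is constant over time models only uⱼ, so it leaves the group-by-time standard error uncorrected. A small simulation (250 runs, change ICC 0.10, 6 versus 6 subgroups) agrees: a mixed model with family and subgroup intercepts rejected 14.8% of the time, and the plain t test on change 14.4%.

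**The case against.** **The ICC is unknown and may be small.** The same two coaches lead every subgroup, which removes differences between coaches. The content is structured and the same in both formats. Web carers work mainly at home with individual feedback. Patients, who supply the eating disorder outcomes, are not described as attending the subgroups, so any clustering in their data is indirect. All of this stands. A reader might infer that the standard errors are certainly too small, but the documents support only the conditional statement. Group dynamics and shared timing remain, however, and the plan gives no reason to take the ICC as zero.

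**The primary contrast is little affected.** This also stands: the pooled comparison with control moves from 5% to between 5.6% and 7.6%. The nonrandomised control group, recruited at other sites, is a greater threat to that contrast.

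**Detail may sit in an unseen analysis plan.** This does not answer the point. Section 2.8 is not silent: it names the model and its factors, and section 2.5 gives a sample size that assumes independence.

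**A stronger reading concerns the unit of randomisation.** Section 2.6 says "randomisation is done blockwise according to the consecutive numbering, in blocks of eight participants in the workshop support group", and likewise for the web format. Because block and subgroup sizes match, a reader might infer that whole blocks of eight went to one format, leaving six randomised units against six. The document does not establish this. The same section has patients and carers allocated after baseline assessment, with blocks used to balance group sizes, which is the ordinary purpose of blocked individual allocation. The point here does not need that reading.

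**A low power baseline.** A two-group test with d = 0.5 and 40 analysed per arm gives only 0.73 (pooled versus control) or 0.61 (workshop versus web) before any clustering. That shortfall comes from changing the test and should not be attributed to clustering.

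**Conclusion.** The concern holds in conditional form. Treatment is given in interacting subgroups, while the stated analysis and the stated power both treat families as independent. If the within-subgroup ICC of change is above zero, standard errors are too small. At assumed ICCs of 0.02 to 0.10 in both formats, the distortion is material for workshop versus web and mild for the primary contrast. With no clustering in the web arm, the workshop versus web error rate is about 7% to 9% at workshop ICCs of 0.05 to 0.10.

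These sizes rest on the assumed ICCs, on subgroups of equal size and, for power, on f = 0.25. The documents do not support a claim that the primary result is seriously compromised by clustering. Severity: should be fixed.

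**What to change.** **Section 2.8.** Analyse T1 adjusted for baseline, and T2 likewise, with a partially nested mixed model: a random subgroup effect in the two SUCCEAT arms only (12 subgroups), residual variance by condition, and Kenward-Roger or Satterthwaite degrees of freedom. If the repeated-measures model is kept, include a random subgroup-by-time effect; a time-constant subgroup intercept is not enough. Report the estimated ICC.

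**Section 2.5.** State that 0.88 power assumes independent families, and give the lower power over a range of ICCs, as in step 5 of the working.

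**Cost.** Rewording of two sections, with no new participants or assessments. The model needs each family's subgroup. The article does not say that this is recorded, so it should be confirmed, although delivery in fixed subgroups should make it recoverable. Confidence intervals become somewhat wider and the stated power less favourable. If the ICC proves negligible, little is lost.
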